### Handling of Subject Withdrawals or Subject Discontinuation of Study Intervention

Given the established safety profile of the intervention there is minimal risk of continued *lesu* use outside the parameters of the study. Therefore, subjects who withdraw or otherwise discontinue participation will not be followed further.

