### Reasons for Withdrawal

Subjects are free to withdraw from participation in the study at any time upon request. An investigator may terminate a study subject’s participation in the study if:

- Any clinical AE, laboratory abnormality, or other medical condition or situation occurs such that continued participation in the study would not be in the best interest of the subject.
- The subject meets an exclusion criterion (either newly developed or not previously recognized) that precludes further study participation. This may include change of residence outside the study area.
- The subject is “lost to follow-up” defined as failure to attend three consecutive study visits and staff are unable to contact by phone or proxy.

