# STUDY SCHEDULE

Each individual’s participation in the study, defined from initial recruitment to the final study visit, is anticipated to take place over a period of approximately 8 months. A complete Schedule of Events is shown in **Appendix A**. Descriptions of each participant encounter are provided below.

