## Time Period and Frequency for Event Assessment and Follow-Up

Unanticipated problems will be recorded in the data collection system throughout the study. The PI will record all reportable events with start dates occurring any time after informed consent is obtained until 7 (for non-serious AEs) or 30 days (for SAEs) after the last day of study participation. At each study visit, the investigator will inquire about the occurrence of AE/SAEs since the last visit. Events will be followed for outcome information until resolution or stabilization.

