## Characteristics of an Adverse Event

### Relationship to Study Intervention

To assess the relationship of an event to the study intervention, the following guidelines are used:

- Related (Possible, Probable, Definite)
  - The event is known to occur with the study intervention.
  - There is a temporal relationship between the intervention and event onset.
  - The event abates when the intervention is discontinued.
  - The event reappears upon a re-challenge with the intervention.
- Not Related (Unlikely, Not Related)
  - There is no temporal relationship between intervention and event.
  - An alternate etiology has been established.

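### Section 4.5.2 stops all follow-up when participation ends, which contradicts the safety windows in Section 8.2; for completers those windows contain no scheduled contact

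*Protocol*

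**What the plan says.** Four parts of the protocol bear on this.

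- **Section 4.5.2** gives a reason, "Given the established safety profile of the intervention there is minimal risk of continued" use of the cloth outside the study, and concludes that "subjects who withdraw or otherwise discontinue participation will not be followed further". It makes no exception for safety.
- **Sections 4.5 and 4.5.1.** Section 4.5 follows participants to closeout, withdrawal of consent or death, and allows the investigator to withdraw someone for safety among other reasons. One ground on which Section 4.5.1 lets the investigator end participation is worded "Any clinical AE, laboratory abnormality, or other medical condition or situation occurs", with the condition that staying in would be against the person's interests.
- **Sections 8.2 and 8.3.1.** Section 8.2 sets the recording window: from consent "until 7 (for non-serious AEs) or 30 days (for SAEs) after the last day of study participation". It adds: "Events will be followed for outcome information until resolution or stabilization". Active enquiry about events is described at study visits only. Among the guidelines for relatedness in Section 8.3.1 is "The event abates when the intervention is discontinued".
- **Sections 6 and 6.5 and Appendix A.** Participation is "defined from initial recruitment to the final study visit", and the final visit is Day 168. Neither Section 6 nor Appendices A1 and A2 list a later contact. The only home encounters under the last column are observation of lesu use and mosquito trapping.

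**The concern.** For the same person, Section 8.2 requires 7 or 30 days of recording plus follow-up of open events, while Section 4.5.2 allows none. Staff who follow 4.5.2 as written breach 8.2.

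The conflict matters most where the investigator ends participation because of an adverse event. Such a mother or child need not have withdrawn consent, so consent does not explain the loss of follow-up. What is at stake is the outcome of the event, the dechallenge information that Section 8.3.1 uses for causality, and any new serious event in the following 30 days. Relatedness also counts elsewhere: the halting rule in Section 8.5 refers to study-related moderate events, and Section 9 asks for prompt reporting of moderate or severe events related to participation.

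Completers have a milder version of the problem. The windows in 8.2 open when participation ends, and by then the last visit at which anyone asks about events has passed. Participants keep the lesus (Section 1.4.2), so contact with the cloth can continue.

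**Working it through.** The protocol gives no figure for this point, so the check compares the rules and then does simple day arithmetic.

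**1. Days of safety follow-up required and allowed**

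| Participant | Section 8.2 requires | Other sections provide |
| --- | --- | --- |
| Investigator ends participation for an adverse event, consent intact | 7 days (non-serious) or 30 days (serious), plus open events to resolution or stabilization | 4.5.2: 0 days. 4.5: follow-up continues, since none of its three end points has occurred, unless this counts as closeout |
| Withdraws consent to further information | Same text | Nothing further can be collected under any rule |
| Stops using the lesu but stays in the study | Same text | Two-weekly visits continue |
| Completes Day 168 | 7 or 30 days after Day 168 | No scheduled contact |

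The first row is a contradiction. The second cannot be repaired and is not a fault. The third is not a problem. The fourth is a gap in planned ascertainment.

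**2. Windows for completers**

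Inputs: final visit on Day 168 (6.5); windows of 7 and 30 days (8.2).

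- Non-serious events: 168 + 7 = Day 175.
- Serious events: 168 + 30 = Day 198.
- Scheduled contacts after Day 168 in Section 6 and Appendices A1/A2: 0.
- Share of the period from lesu issue (Day 0) to the end of the serious-event window that has no scheduled contact: 30/198 = 15.2%.

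**3. Rough scale of early departure**

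Input: 48 of 50 pilot pairs completed, and the two that did not were replaced (pilot study section).

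- 2/50 × 400 = 16 pairs. With the replacements in the denominator, 2/52 × 400 = 15.4 pairs.

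This covers departure for any reason, including withdrawal of consent. Both pilot dropouts completed only baseline activities, and nothing ties either to a reaction. Pilot follow-up was 12 weeks, against 24 here. The figure therefore does not estimate withdrawals due to adverse events.

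**4. What reaches the planned safety analysis**

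Section 10.3.2 plans, for each arm, a one-sided 95% Clopper-Pearson upper limit for the probability of a serious event. With x participants affected out of n, the limit is the 0.95 quantile of Beta(x + 1, n − x). Assuming n = 200 per arm:

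- x = 0: 1.49%
- x = 1: 2.35%
- x = 2: 3.11%

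The limit counts occurrence, not outcome. A serious event that leads to withdrawal happened during participation and is already in x. Only a new serious event, after withdrawal or after Day 168, can be missing. If one were missed, the limit would be too low by about 0.8 to 0.9 percentage points (2.35 − 1.49 = 0.86; 3.11 − 2.35 = 0.76).

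**The case against.** The strongest reply has four parts.

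- **Stopping the cloth is not leaving the study.** The heading of 4.5.2 mentions discontinuing the intervention, and a reader might infer that anyone who puts the lesu aside is no longer observed. The operative sentence covers only those who end participation, and Section 10.3 analyses pairs regardless of use. A mother who stops using the lesu but stays keeps her visits, so whether an event abates can still be seen. This stands; the causality concern is confined to people whose participation ends.
- **The triggering event is counted.** A reader might infer that the worst reactions vanish and that the treated arm looks safer. The documents do not support that. The event is recorded before withdrawal, and the absence of contact after Day 168 is the same in both arms. Only outcome, dechallenge information and new events are exposed.
- **No safety decision turns on one or two events.** Section 10.3.2 is descriptive and sets no threshold, so it cannot be said that a missed event would change the safety conclusion. This also stands.
- **Spontaneous reporting exists.** Participants hold a card with study telephone contacts (6.2), staff hold participants' details and work with community health workers (4.3.4), and a Manual of Procedures, not shown, may add a call. So the windows for completers are not impossible to deliver; they merely have no planned contact.

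None of this removes the conflict between 4.5.2 and 8.2. Nor does the low-risk rationale in 4.5.2, because 8.2 covers the same product and still asks for follow-up.

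**Conclusion.** The point holds in a limited form. Sections 4.5, 4.5.2 and 8.2 contradict each other for participants whose participation ends early without withdrawal of consent to contact, and most seriously for those removed because of an adverse event. What would be lost is the outcome of the event, the dechallenge information, and any new serious event within 30 days. For completers, the windows to Day 175 and Day 198 have no scheduled contact, so capture is passive.

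The size is modest. About 16 of 400 pairs is a rough scale for all early departures, assuming that the pilot's non-completion carries over; the number due to reactions cannot be derived from the document. The gap after Day 168 touches every completer. Its effect on the limits in 10.3.2 is under one percentage point per missed participant at these low counts, assuming 200 per arm.

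This should be corrected before the safety results are interpreted. It does not bear on the primary efficacy comparison.

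**What to change.** **Early departures.** Reconcile 4.5, 4.5.2 and 8.2. State in 4.5.2 that ending participation stops study visits and efficacy follow-up, but that the recording windows and event follow-up of 8.2 still apply unless consent to further contact is withdrawn. Use the telephone and community health worker procedure already in 4.3.4. The cost is a short amendment and a few contacts, on the order of 16 pairs if the pilot rate holds.

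**Completers.** Choose one of two options and write it down:

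- Add a brief telephone or community health worker contact at the end of the 30-day window to 6.5 and to Appendices A1 and A2. The cost is staff time for up to about 400 calls.
- State in 8.2 that events after Day 168 are captured by spontaneous report only, so that the limits in 10.3.2 are read accordingly. This costs one sentence, but ascertainment in the window stays passive.

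Both changes concern the collection of safety data only and leave the clinical handling of any event as it is.

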## Premature Termination or Suspension of Study

This study may be suspended or prematurely terminated if there is sufficient reasonable cause. Written notification, documenting the reason for study suspension or termination, will be provided by the suspending or terminating party to the sponsor and relevant regulatory authorities. If the study is prematurely terminated or suspended, the principal investigator (PI) will promptly inform the institutional review board (IRB) and will provide the reason(s) for the termination or suspension.

Circumstances that may warrant termination include, but are not limited to:

- Determination of unexpected, significant, or unacceptable risk to subjects.
- Insufficient adherence to protocol requirements.
- Data that are not sufficiently complete and/or evaluable.

# STUDY INTERVENTION

## Study Product Description

Permethrin is a synthetic derivative of the naturally occurring pyrethrins found in chrysanthemum flowers. Permethrin acts on nerve cell membranes of the mosquito to disrupt the sodium channel current that regulates the polarization. This results in delayed repolarization, paralysis, and ultimately death of the mosquito. Permethrin also has a modest repellent effect, which may prevent biting even when mosquitoes are resistant to the killing effect [27]. Permethrin has been widely used in LLINs to prevent malaria in endemic areas and is the only repellant currently registered to treat fabric in the United States [36].

Permethrin treated clothing has a well-established safety record. Studies conducted among military personnel wearing permethrin-treated clothing demonstrated that exposure from chronic daily wear correlates with duration of exposure and is higher than the background exposure among the general population, but calculated daily exposures were still lower than exposure from topical pharmaceutical application [24, 25].

In data taken from studies of the topical permethrin formulation used to treat pregnant women with scabies or lice, no increase in the risk of congenital abnormalities was noted among children exposed *in utero* [37, 38]. The FDA classifies permethrin cream as Class B during pregnancy and the WHO considers permethrin compatible with breastfeeding [39].

### Acquisition

All permethrin will be obtained directly from the manufacturer (Sawyer Products, Safety Harbor, FL). *Lesus,* of all the same material and design, will be obtained from local vendors.

### Formulation, Packaging, and Labeling

Permethrin will be acquired as 40% concentrate from the manufacturer available in 250 mL bottles packed in cases of 12 bottles. Labeling of individual bottles will be “INSECT/ARTHROPOD REPELLENT PROTECTIVE TREATMENT FOR MILITARY BATTLE DRESS UNIFORM*.”* A safety data sheet (MSDS 002778A) will accompany each case of bottles [40].

### Product Storage and Stability

This material is not regulated by the U.S. Department of Transportation as a hazardous material. General storage instructions are to not use or store near heat, sparks, open flame, or any other ignition sources. Staff will wear chemical-resistant gloves such as Barrier® laminate, neoprene rubber, nitrile rubber, or Viton® when handling, along with a long-sleeved shirt, long pants, socks, and shoes. The product will be stored in a cool, dry place, under lock and key. All containers will be kept closed. The storage area will be posted as a pesticide storage area with instruction to keep away from heat, sparks, open flame, and any other ignition sources as well as strong acids, bases, and oxidizers. All product will be utilized prior to the labeled expiration date.

## Dosage, Preparation, and Administration of Study Product

Prior to application, permethrin concentrate will be diluted to 0.5% concentration. This will be achieved by adding 12.5 mL of 40% concentrate and adding water until a total volume of 1 L is reached (i.e., mixing ratio is 1.25 w/w concentrate and 98.75 w/w water).

*Lesus* of participants randomized to the intervention group will be soaked in 0.5% permethrin in accordance with the manufacturer’s instructions. In brief, *lesus* will be rolled tightly and secured with rubber bands or ties. The rolled *lesus* will be placed in 1 gal plastic bags and approximately 100 mL of permethrin will be added. The bag will be gently massaged until the cloth is completely soaked. After 1 hour, the *lesu* will be removed, unrolled, and hung to dry in an area that is not exposed to direct sunlight.

Re-treatments occur every 4 weeks of study participation. *Lesus* of participants assigned to the control group will follow similar procedures, but re-treatment will take place with water only (i.e., sham treatment).

## Modification of Study Product Administration for a Subject

No dose adjustments or modifications to the frequency of re-treatment are planned.

## Accountability Procedures for the Study Product

Two *lesus* will be provided to each participant at the first clinic visit. Participants will be asked to bring study *lesus* to each visit for visual inspection.

## Assessment of Subject Compliance with Study Product Administration

Staff will instruct participants that the provided *lesus* should be used exclusively during the study period. Participants will be asked to maintain a written log of daily *lesu* use and washing. These logs will be returned to study staff at the bi-monthly study visits.

In addition, staff will take small punches of *lesus* at the 2-, 4-, and 6-month visits. Harvested fabric swatches will be placed in individual mylar bags and stored in an opaque container at 20^o^ C until transport to the [name] lab at East Carolina University. Swatches will be transferred to individual 60 mL amber glass vials containing 40 mL acetone and soaked for 6 hours to elute permethrin. A portion of the extract (1 pL) will be analyzed directly by capillary GC with flame ionization detector using an Agilent GC 6850 in accordance with previously published protocols [35, 41].

## Concomitant Medications/Treatments

Participants will be asked to document frequency of LLIN use each night on the daily log as noted in Section 5.5. Staff will also ask about any treatments of the home environment such as IRS. Staff will also ask participants about use of any medications with antimalarial effects including, but not limited to:

- Antimalarials:
  - Artemisinin combination therapies (e.g., artemether/lumefantrine)
  - Quinine
  - Sulfadoxine-pyrimethamine
  - Chloroquine
- Antibiotics with antimalarial properties
  - Doxycycline
  - Cotrimoxazole

## Administration of Intervention

Treatment of *lesus*, either with permethrin or sham, will take place during in-person visits. No treatments or re-treatments will take place outside this setting. Study staff responsible for treatment and re-treatment, who will be unblinded to the intervention, will confirm the group assignment against randomization table prior to treatment and re-treatment. During treatment or sham treatment, each ziploc bag will be labeled with the study ID to prevent confusion.

## Procedures for Training Interventionists and Monitoring Intervention Fidelity

Having worked on the pilot study, many study team members are experienced with many of the methods and procedures. Prior to implementation, however, we will conduct a week-long training event, which will review procedures for treatment of *lesus*. In addition to didactic instruction, we will conduct a practical exercise. All staff will be required to demonstrate proficiency with the process.

## Assessment of Subject Compliance with Study Intervention

In addition to daily use logs, we will ask participants for permission to perform intermittent, direct observation of daily use. Study staff will visit participants households and observe use throughout the day with particular emphasis on early morning and early evening hours when individuals are not yet under the cover of a LLIN, but *Anopheles* mosquitoes are likely active in the peri-domestic space. Participants will be notified when selected for observation and scheduled for a day that is convenient.

# STUDY SCHEDULE

Each individual’s participation in the study, defined from initial recruitment to the final study visit, is anticipated to take place over a period of approximately 8 months. A complete Schedule of Events is shown in **Appendix A**. Descriptions of each participant encounter are provided below.

## Screening

### Information Sessions

Initial recruitment, which will be conducted by local CHWs, will target all women with children under 18 months of age residing in villages located within 2 km of a study clinic. Potentially eligible women will be invited to attend an information meeting, where staff will describe the study aims, methods and anticipated risks/benefits of participation in a group setting. Women who are interested in participating will move to a private area where they will have an opportunity to ask additional questions. Study staff will the screen women based on responses to eligibility questions. We will not review medical records or perform confirmatory diagnostic testing (e.g., HIV) at this visit. If the patient meets criteria, staff will record the individual’s full name, household location, contact information, and schedule a household visit within the next 21 days.

### Final Screening (Day -21 to -7)

On the scheduled date, a study staff member will travel to the household, review the consent form, answer any questions, and ask the individual to provide written consent for participation. The consent form will include language stating that a negative rapid HIV test is required for before enrollment and that if the result is positive, the individual will not be eligible to participate (i.e., screen failure), but will be immediately linked to care. If negative, this will be immediately followed by the household survey.

## Household Survey

After enrollment is complete, study staff will:

- Record the household location using a handheld GPS device or smart phone.
- Document demographic and household characteristics via a questionnaire modified from the most recent Demographic and Health Survey [21].
- Perform a malaria RDT on both mother and child and if positive, receive weight-based treatment with AL, which is first-line therapy for uncomplicated malaria in Uganda [42].
- Issue a new LLIN (Permanet® 2.0, Vestergaard S.A., Switzerland) with guidance that it should be utilized to protect the child.
- At the conclusion of the survey, study staff will make an appointment date for the first clinic visit and provide the participant with an identification card, including the unique study ID number and telephone contacts.

## Baseline Clinic Visit (Day 0)

Participants will be scheduled for a baseline visit at either the Bugoye or Mukathi Level III Health Center. During the baseline visit, study staff will:

- Confirm participant identify and study number.
- Administer a questionnaire reviewing changes in medical history since the household visit.
- Measure and record vital signs, including:
  - Child’s height, weight and MUAC
  - Child’s axillary temperature
- Have 3–4 mL of blood drawn by venous phlebotomy from the child to:
  - Perform testing for Hb concentration
  - Create DBS for qPCR testing at a later date.
  - Store sera for future seroprevalence studies of vector-borne disease
- Have 6–8 mL of blood drawn by venous phlebotomy from the mother to:
  - Perform testing for Hb concentration
  - Create DBS for qPCR testing at a later date.
  - Store sera for future seroprevalence studies of vector-borne disease
- Issue the permethrin-treated or untreated *lesus* (2) according to randomization
- Provide an in-kind incentive (e.g., sugar, soap, cooking oil) and travel supplement, the combined value of which is estimated to be approximately $4–5 per visit.
- Provide a card to remind them of the date and time of their next visit.

## Bi-Monthly Visits (Days 14, 28, 42, 56, 70, 84, 98, 112, 126, 140, 154)

Participants will be scheduled in advance for a follow-up visit at the same health center every 2 weeks. Activities at each visit include:

- Confirm participant identify and study number.
- Administer questionnaire reviewing changes in medical history since the last visit.
- Record adverse events as reported by subject or observed by investigator.
- Measure and record vital signs, including:
  - Child’s height, weight and MUAC
  - Child’s axillary temperature
- Draw 50 µL capillary blood by finger-prick or heel stick from the child to create DBS for qPCR testing at a later date.
- Provide an in-kind incentive (e.g., sugar, soap, cooking oil) and travel supplement, the combined value of which is estimated to be approximately $4–5 per visit.
- Provide a card to remind them of the date and time of their next visit.

The following visits will have additional activities:

- **Visits on Day 28, 56, 70, 98, 126, 154**: Retreatment of *lesus*
- **Visits on Day 56 and 98**: Punch from *lesus* to measure permethrin content
- **Visit on Day 84**: Venous blood draws (mother/child) instead of capillary to:
  - Perform testing for Hb concentration
  - Create DBS for qPCR testing at a later date.
  - Store sera for future seroprevalence studies of vector-borne disease

